#### Primary Efficacy End Points

##### Analysis of Primary End Points

Progression-free survival and hepatic progression-free survival will be compared between the control and TARE groups using log-rank tests. The HR and 2-sided 95% CI will be computed. Kaplan-Meier curves will also be produced.

##### Interim Analyses of Primary End Point of Progression-Free Survival

The first interim analysis is planned at 172 progression-free survival events. Progression-free survival will be compared between treatment groups using a log-rank test converted to a z-score and compared with the nominal critical value of 2.372 based on the rho family error spending function corresponding to a one-sided *P* ≤.0088, allowing the study to be stopped early for efficacy, in which case hepatic progression-free survival will be tested at the same boundary as progression-free survival using a log-rank test converted to a z-score.

A second interim analysis is planned at 241 progression-free survival events, where progression-free survival will be compared between treatment groups using a log-rank test converted to a z-score and compared with the nominal critical value of 2.330 based on the rho family error spending function corresponding to a one-sided *P* ≤.0099, allowing the study to be stopped early for efficacy. If the study is stopped early for progression-free survival at the second interim analysis, hepatic progression-free survival will be tested using the boundary derived based on an incremental alpha of .0057. This boundary will account for the correlation between the z-score for progression-free survival at the first interim analysis and the z-score for hepatic progression-free survival at the second interim analysis, which is determined by the observed number of hepatic progression-free survival events at the first interim analysis and the cumulative number of hepatic progression-free survival events observed at the second interim analysis.

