### Planned Statistical Analysis

#### Sample Size Estimate

The study is a phase 3 adaptive trial, comprising a group sequential design with 2 interim analyses. The study could be stopped early for efficacy at an interim analysis based on superiority in progression-free survival but not hepatic progression-free survival.

The study is designed to detect a 2.5-month increase in median progression-free survival, from 6 months in the control group to 8.5 months in the TARE group (hazard ratio [HR] 0.71), and a 3.5-month increase in median hepatic progression-free survival time, from 6.5 months in the control group to 10 months in the TARE group (HR 0.65). On the basis of simulations, the power to detect the target difference in either progression-free survival or hepatic progression-free survival is >90%, and the power to detect the target difference in each end point alone is >80%, using log-rank tests.

The analysis of progression-free survival will be based on a group sequential design with 2 interim analyses at 50% and 70% of the required total number of 344 progression-free survival events with a stopping boundary defined by the rho family error spending function with ρ=1.5 [24]. It is estimated that a maximum of 420 patients will need to be recruited over 36 months, with a 1-year additional follow-up period, allowing for 10% of patients lost to follow-up and for whom a date of progression or death is not recorded. Although the forecasted accrual period has been increased to 60 months, this does not increase the number of patients required or affect the statistical power of the study because both the power and the timing of the interim and final analyses are based on the number of progression-free survival events rather than the number of patients. The Hochberg procedure will be used to control type 1 error for the 2 primary end points at the final analysis [25].

A simulation study, assuming that progression-free survival and hepatic progression-free survival have a correlation between 0.3 and 0.8, showed that the power to detect the target difference in either median progression-free survival (ie, HR 0.71) or median hepatic progression-free survival (ie, HR 0.65) is >90%, and the power to detect the target difference in progression-free survival or hepatic progression-free survival alone is >80%. The simulation study also demonstrated control of type 1 error at the nominal one-sided level of 0.025.

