##### Final Analysis of Primary End Points of Progression-Free Survival and Hepatic Progression-Free Survival

The final analysis is planned at 344 progression-free survival events. The Hochberg procedure will be used to control type 1 error for the 2 primary end points [25]. Whichever of progression-free survival or hepatic progression-free survival that has the larger *P* value will be compared between treatment groups using a log-rank test converted to a z-score and compared with the nominal critical value of 2.312 with a corresponding one-sided *P* ≤.0104 required to declare a statistically significant improvement in hazard rate for this end point. To ensure that type 1 error is controlled for both primary end points, this boundary is based on the incremental alpha of .0104 instead of the *P* value scale boundary of .0168, using the rho family error spending function with ρ=1.5.

According to the Hochberg procedure, if the primary end point with the larger *P* value is statistically significant, then the other primary end point is also statistically significant. However, if the primary end point with the larger *P* value is not statistically significant, then the other primary end point will be compared between treatment arms using a log-rank test converted to a z-score and compared with the nominal critical value of 2.562 based on the rho family error spending function, with a corresponding one-sided *P* ≤.0104/2=.0052 required to declare a statistically significant improvement in hazard rate for this end point.

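### The alpha increment for hepatic PFS at the second interim is printed as .0057, but the plan's own spending function and boundaries give .0058

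*Protocol article*

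**What the plan says.** Under Sample Size Estimate, the PFS analysis is group sequential, with "2 interim analyses at 50% and 70% of the required total number of 344 progression-free survival events" and a "stopping boundary defined by the rho family error spending function with ρ=1.5". The same section reports that simulation showed "control of type 1 error at the nominal one-sided level of 0.025".

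The section on the interim analyses of PFS puts the looks at 172 and 241 events. At the first look the log-rank z-score is "compared with the nominal critical value of 2.372 based on the rho family error spending function", "corresponding to a one-sided *P* ≤.0088". At the second look the critical value is 2.330, with one-sided P of .0099. If PFS stops the trial at that second look, HPFS is then tested "using the boundary derived based on an incremental alpha of .0057". The critical value itself is worked out later, from the correlation between the first-look PFS z-score and the second-look HPFS z-score, using observed HPFS event counts.

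For the final analysis the article says that "this boundary is based on the incremental alpha of .0104", in place of the P-value-scale boundary of .0168.

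**The concern.** An error-spending design fixes the alpha available at each look once the spending function, the total alpha and the information fractions are given. The article gives all three, so the second-look increment can be calculated and is not a free choice. The printed .0057 differs from the calculated value in the fourth decimal, while the neighbouring figures agree with it.

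The figure is operative. On the path where the trial stops at the second interim, the HPFS threshold is derived directly from it. A statistician who programs from the spending function and one who programs from the printed increment would reach slightly different thresholds for a primary end point. The same section would then carry two second-look alphas: one implied by the 2.330 boundary and one printed for HPFS.

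**Working it through.** **Inputs, all from the article**

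- One-sided alpha .025; ρ = 1.5; looks at 50% and 70% of 344 PFS events (Sample Size Estimate).
- Looks at 172 and 241 events; boundaries 2.372 (P .0088) and 2.330 (P .0099); HPFS increment .0057 (interim analyses section).
- Final increment .0104 and P-scale boundary .0168 (final analysis section).

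**Formula.** Cumulative spending is α(t) = .025 × t^1.5, and the increment at look 2 is α(t₂) − α(t₁). Boundaries are solved from the joint normal distribution with corr(Z₁, Z₂) = √(t₁/t₂).

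**Step 1: reproduce the plan's other figures (t = .5, .7, 1)**

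| Quantity | Article | Recomputed |
|---|---|---|
| Look 1 alpha | .0088 | .025 × .5^1.5 = .008839 |
| Look 1 boundary | 2.372 | 2.3723 |
| Look 2 boundary | 2.330 | 2.3303 |
| Look 2 nominal P | .0099 | .009895 |
| Final increment | .0104 | .025 − .014642 = .010358 |
| Final P-scale boundary | .0168 | .016773 (z = 2.125) |
| **Look 2 increment** | **.0057** | **.014642 − .008839 = .005803** |

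Only the last row fails.

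**Step 2: use the exact event count.** At t₂ = 241/344 = .7006, α(t₂) = .014660. The increment is .014660 − .008839 = .005821, again .0058. The boundary is 2.3297 (P .0099).

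**Step 3: work back from the printed boundaries.** P(Z₁ < 2.372, Z₂ ≥ 2.330) with correlation √(172/241) = .8448 is .00581. Moving both boundaries across their rounding ranges (2.3715 to 2.3725 and 2.3295 to 2.3305) gives .00580 to .00583, which never rounds to .0057.

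**Step 4: look for a reading that yields .0057.** Each candidate breaks another printed figure.

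| Variant | Look 2 increment | What it breaks |
|---|---|---|
| Look 2 at 240 events | .00573 | boundary 2.333, P .0098; article has 241 events, 2.330, .0099 |
| Look 1 at 173 events | .00574 | z 2.369, P .0089; article has 172 events, 2.372, .0088 |
| ρ = 1.4 | .0057 | look 1 alpha .0095; article has .0088 |

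Conversely, an increment of .0057 with the other inputs as stated needs a look 2 PFS boundary of 2.3353 (70%) to 2.3355 (241 events), P .0098.

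**Step 5: effect on the HPFS threshold.** The article gives no HPFS event counts, so the counts below are assumptions. The first-look boundary is held at 2.372 and the correlation is the square root of the ratio of the counts.

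| Assumed HPFS events, look 1 / look 2 | Critical z at .0057 | Critical z at .0058 | Difference |
|---|---|---|---|
| 162 / 229 | 2.338 (P .0097) | 2.333 (P .0098) | .005 |
| 100 / 170 | 2.385 (P .0086) | 2.379 (P .0087) | .005 |

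**The case against.** Nobody can defend .0057 as a correct rounding of the planned increment, but four points on the other side deserve a hearing.

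- **The total proves little.** The printed increments add to .0088 + .0057 + .0104 = .0249, which looks like a budget that does not close. But at exactly 241/344 the correctly rounded increments are .0088, .0058 and .0103, and these also add to .0249. This point stands, so the case rests on Steps 1 to 3 and not on the sum.
- **The other figures match only under one convention.** The final increment is .0104 at t = .70 but .0103 (.01034) at 241/344. At 240 events both .0057 (.00573) and .0104 (.01043) appear. Truncating 240.8 events to 240 for this one number is therefore a plausible source, though it cannot be shown. That may explain the figure but does not justify it, because 240 contradicts the stated 241 events, the 2.330 boundary and P .0099. The increment rounds to .0058 under both the 70% and the 241-event convention.
- **The HPFS correlation might account for the difference.** It does not. The correlation converts an increment into a critical value, and the article gives the increment as a fixed input to that step.
- **The practical effect is minimal.** This is true. The unknown HPFS event counts move the critical value by up to about ten times as much as the disputed digit (2.338 to 2.385 over the assumed counts above), and only an HPFS P value within about .0001 of the threshold could change side.

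**Conclusion.** The figure is wrong as written: the increment should be .0058. This follows from the article's own inputs and rests on no outside assumption; only the illustrative HPFS critical values depend on assumed event counts.

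The error is minor. About .0001 of the .025 is left unspent, and HPFS faces a critical value about .005 higher on the z scale than the spending function allows. The direction is conservative, so the discrepancy does not raise type 1 error. It matters only if the trial stops for PFS at the second interim. PFS testing, the final analysis and the sample size are untouched. This check covers the value of the increment only, not whether the HPFS testing scheme as a whole controls error.

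**What to change.** Replace .0057 with .0058 in the description of the second interim analysis. If the statistical analysis plan, which was not available, carries the same figure, correct it there too.

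A more durable wording defines the increment by rule: ρ = 1.5 cumulative spending at the observed PFS event fraction, minus the unrounded alpha spent at the first look. The subtraction should not use the rounded .0088: at 241 events that gives .014660 − .0088 = .00586, which would print as .0059. The plan should also say whether printed values use the nominal 70% or 241/344, since the final increment rounds to .0104 under one and .0103 under the other.

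The cost is one figure, or one sentence if the rule is adopted. No boundary for PFS, event target or sample size changes. The correction should be made before second-interim results are unblinded.

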##### Final Analysis of Primary End Points of Progression-Free Survival and Hepatic Progression-Free Survival

The final analysis is planned at 344 progression-free survival events. The Hochberg procedure will be used to control type 1 error for the 2 primary end points [25]. Whichever of progression-free survival or hepatic progression-free survival that has the larger *P* value will be compared between treatment groups using a log-rank test converted to a z-score and compared with the nominal critical value of 2.312 with a corresponding one-sided *P* ≤.0104 required to declare a statistically significant improvement in hazard rate for this end point. To ensure that type 1 error is controlled for both primary end points, this boundary is based on the incremental alpha of .0104 instead of the *P* value scale boundary of .0168, using the rho family error spending function with ρ=1.5.

According to the Hochberg procedure, if the primary end point with the larger *P* value is statistically significant, then the other primary end point is also statistically significant. However, if the primary end point with the larger *P* value is not statistically significant, then the other primary end point will be compared between treatment arms using a log-rank test converted to a z-score and compared with the nominal critical value of 2.562 based on the rho family error spending function, with a corresponding one-sided *P* ≤.0104/2=.0052 required to declare a statistically significant improvement in hazard rate for this end point.

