### Randomization and Stratification

Eligible patients are randomized on day 0 in a 1:1 ratio to either the control group or the TARE group. If the study is not stopped early for efficacy, approximately 210 patients will be randomized to each group. To randomize eligible patients, the study site contacts the central randomization office where randomization will be determined using assignment by a computer-generated randomization scheme. Upon randomization, each patient is assigned an identity code. To ensure that treatment groups are balanced, patients are stratified at randomization based on the extent of liver involvement (unilobar vs bilobar disease), type of first-line chemotherapy (oxaliplatin-based vs irinotecan-based), and KRAS status (wild type vs mutant). Additional factors permitting covariate analysis are captured at randomization but are not stratification criteria. These factors have been defined based on the planned covariate analyses. Patients randomized to either the control or the TARE group who are unable to receive their planned study treatment continue to be followed under their assigned study group for the purpose of the intent-to-treat analysis.

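### After HPFS has won at the final analysis, PFS is still held to one-sided P ≤ .0104, although its own final boundary of .0168 would keep error within .025; about 2 to 3 points of PFS power are lost.

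*Protocol article*

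**What the plan says.** Under Sample Size Estimate, PFS follows a group sequential design with "2 interim analyses at 50% and 70% of the required total number of 344 progression-free survival events", using a rho-family spending function with ρ = 1.5. For the two primary end points, "The Hochberg procedure will be used to control type 1 error for the 2 primary end points at the final analysis". A simulation is reported to have shown "control of type 1 error at the nominal one-sided level of 0.025".

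The interim section gives PFS boundaries of z 2.372 (P .0088) at 172 events and z 2.330 (P .0099) at 241 events. HPFS cannot stop the trial; it is tested at an interim only if PFS stops the trial there.

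The section on the final analysis, at 344 PFS events, sets two steps:

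- The end point with the larger P value needs z 2.312 (P ≤ .0104). If it succeeds, both are significant.
- If it fails, the other end point needs z 2.562 (P ≤ .0052).

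The stated reason for using .0104 and not the P-scale boundary of .0168 is: "To ensure that type 1 error is controlled for both primary end points, this boundary is based on the incremental alpha of .0104". No further step follows for the end point that failed at .0104.

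**The concern.** Suppose HPFS has P = .001 and PFS has P = .015 at the final analysis. PFS has the larger P value and fails at .0104. HPFS then wins at .0052, and PFS is declared not significant, however small the HPFS P value is. Yet .015 lies inside the boundary that PFS would have had as the only primary end point, after interim looks that have already charged PFS for its early alpha.

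The protection that .0104 gives is against a false claim when neither end point has improved. Once HPFS has been declared significant, that situation has been rejected, and the remaining question is whether PFS alone is null. For that question the plan already holds a complete level-.025 test: 2.372, 2.330, then 2.125. At stake is the second primary claim, on the end point with which the trial began as its sole primary.

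**Working it through.** **Inputs.** One-sided alpha .025; ρ = 1.5; looks at 172, 241 and 344 PFS events; allocation 1:1 ("Eligible patients are randomized on day 0 in a 1:1 ratio"). The PFS target is "from 6 months in the control group to 8.5 months in the TARE group (hazard ratio [HR] 0.71") and the HPFS target is "from 6.5 months in the control group to 10 months in the TARE group (HR 0.65"). The PFS–HPFS correlation is 0.3 to 0.8, as in the plan's own simulation. The article does not give the number of HPFS events at the final analysis. I assumed 260, 300 and 330, with the same information fractions as PFS.

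**1. Reproducing the plan's boundaries.** Cumulative spending is .025 × t^1.5.

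- t = 0.5: .00884
- t = 0.7: .01464, increment .00580 (the plan prints .0057, which does not affect this point)
- t = 1: .02500, increment .01036, printed as .0104

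Solving the trivariate normal with correlations √(ti/tj) gives z = 2.372, 2.330 and 2.125 (P .0088, .0099, .0168). Also z(.0104) = 2.312 and z(.0052) = 2.562. The printed boundaries all reproduce.

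**2. PFS error when only the PFS null is true.**

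- Looks 2.372 / 2.330 / 2.312: .0202
- Looks 2.372 / 2.330 / 2.125: .0250

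The first figure is the most the plan's rule can spend on PFS, so about .0048 of its .025 is left unused.

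**3. Error control with the added step** (PFS tested at 2.125 only if HPFS has won at .0052).

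- *Both nulls true.* The step acts only after HPFS has already been falsely rejected, so it adds no new familywise error. The bound stays .0088 + .0058 + .0104 = .0250. Simulation (2,000,000 draws per scenario) gives .0217, .0215 and .0201 at correlation 0.3, 0.5 and 0.8, with and without the step.
- *Only the HPFS null true.* No HPFS decision changes.
- *Only the PFS null true.* Error is at most .0250, from item 2.

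**4. PFS power.** Drift is √(344/4) × |ln 0.71| = 9.274 × 0.3425 = 3.176. Tested alone, PFS has power 83.1% with a last boundary of 2.312 and 86.7% with 2.125. The difference, 3.55 points, is the ceiling, reached if HPFS always wins.

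Under the full two-end-point rule, PFS power without and with the step is:

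| Correlation | HPFS events | Plan | With step | Gain (points) |
|---|---|---|---|---|
| 0.3 | 260 | 82.38% | 85.01% | 2.6 |
| 0.3 | 300 | 82.61% | 85.54% | 2.9 |
| 0.3 | 330 | 82.76% | 85.84% | 3.1 |
| 0.5 | 260 | 82.23% | 84.69% | 2.5 |
| 0.5 | 300 | 82.55% | 85.34% | 2.8 |
| 0.5 | 330 | 82.75% | 85.73% | 3.0 |
| 0.8 | 260 | 82.30% | 84.42% | 2.1 |
| 0.8 | 300 | 82.73% | 85.37% | 2.6 |
| 0.8 | 330 | 82.88% | 85.84% | 3.0 |

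The probability that at least one primary end point is significant is the same in both columns in every scenario (for example 94.17% at correlation 0.5 and 300 HPFS events).

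**5. On the hazard-ratio scale.** With 344 events the observed PFS hazard ratio needed is about exp(−2.312/9.274) = 0.779 under the plan and exp(−2.125/9.274) = 0.795 with the step. Results between these two values are the ones affected.

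**The case against.** The strongest reply is that nothing is broken. The rule is fully specified, its reason is stated, and it controls error. The plan claims that "the power to detect the target difference in progression-free survival or hepatic progression-free survival alone is >80" percent, and the PFS figure of 82–83% under the rule as written agrees with that. Success is defined as at least one significant primary end point, and the added step acts only after one has won, so the chance of success does not move. All of this stands. It makes the point one of efficiency, and limits its weight.

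Three stronger readings are tempting, and the documents do not support them:

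- *That type 1 error is inflated.* It is not; the rule errs on the safe side.
- *That .0104 is needless altogether and .0168 could replace it.* Using .0168/.0084 from the opening Hochberg step gives a joint-null error of about .0267 at correlation 0.3 and .0263 at 0.5. The plan's caution is right for that step.
- *That HPFS deserves the mirror-image step.* The gain there is under 0.5 points, and its boundary would need HPFS event counts that the article does not give.

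Nor does the relaxation leave every error rate where it was. With only the PFS null true, error rises from .0202 to .0250; what is unchanged is the .025 limit and the joint-null error.

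A last objection is timing. Enrollment has ended, the first interim analysis has been reviewed, and the trial is open-label. Loosening a primary threshold now needs justification. That is a real but small cost if the change is fixed before final unblinding.

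**Conclusion.** The point holds as a loss of efficiency. The final-analysis rule denies a PFS claim with one-sided P between .0104 and .0168 after HPFS has won at .0052, and the .025 limit does not require it. Allowing the claim is uniformly more powerful and changes no look, event count or sample size.

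The size is about 2 to 3 points of PFS power (2.1 to 3.1 over the scenarios tried, ceiling about 3.5). It rests on the design hazard ratios, proportional hazards, a correlation between the test statistics of 0.3 to 0.8, and HPFS event counts that I had to assume. The rule as written remains valid.

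**What to change.** Keep the Hochberg step at .0104/.0052 as the gate. Add one sentence: if HPFS is significant at P ≤ .0052 while PFS has P > .0104, PFS is then tested against its own rho-family final boundary, z 2.125 (P ≤ .0168). Compute that boundary unrounded from the PFS event counts at the three looks; at 172/241/344 it is 2.1257, so the printed 2.125 is slightly rounded down. Leave the HPFS rule as it is.

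The cost is a documented amendment with its rationale and a rerun of the type 1 error simulation under the new rule. Because the first interim analysis has already taken place, it should be fixed before final unblinding.
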